### Sample size calculation

The study conducted by Blackman demonstrated that the 12-week ulcer healing rate in the standard treatment group for diabetic foot ulcers was 42.8%, whereas the wound healing rate in the group receiving TOT was significantly higher at 85.2% [17]. Our previous research documented a wound healing rate of 69% in the standard treatment group for diabetic foot ulcers [22]. Assuming a baseline wound healing rate of 60% in the standard treatment group over a 12-week period, it is hypothesized that the incorporation of TOT would result in a 30% relative improvement in the wound healing rate, i.e., from 60% to 78%. This hypothesis will be evaluated using a two-sided test with a significance level (α) of 0.05 and a statistical power (1-β) of 0.8. Sample size estimation, conducted using PASS 15 software and based on the methodology for comparing two-group proportions in a randomized controlled trial, indicated that each experimental and control group should comprise approximately 100 participants, totaling 250 participants when accounting for an expected dropout rate of approximately 20%.

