### Randomization and allocation concealment

The eligible participants will be randomly assigned in a 1:1 ratio to either receive TOT or sham oxygen therapy. Additionally, all subjects will receive standard wound care as prescribed by their attending physician. The random sequence will be generated by a researcher utilizing R software with the simple randomization method. A designated technician will oversee the sequence numbers and monitor the treatment procedures. Both the attending physician and participants will remain blinded to the specific oxygen therapy protocol.

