#### Secondary outcome.

Rate of ulcer area reduction: percent change in wound size after 12 weeks of treatmentTime to ulcer healing: duration until complete wound closureOne-year ulcer recurrence rate: proportion of ulcers that recur within one-year post-healingAmputation rate at 12 weeks: incidence of amputation within the first 12 weeksVAS score: Visual analogue scale for pain assessmentWound-QoL: Questionnaire assessing quality of life in patients with chronic wounds

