### Follow-up

Patients will be randomly allocated to either the treatment group or the control group and will receive the respective interventions until complete wound healing occurs or for a maximum duration of 12 weeks. Digital photography will be employed to systematically document images on a weekly basis. The researchers will determine whether the outcomes were reached. Because of the objective feature, the outcome assessment for wound healing will not be blinded or centralized. The Image J software will be utilized to quantitatively measure the area of the foot ulcer during each debridement and dressing change procedure. The total follow-up period will span one year, with evaluations conducted at 4-, 8-, 12-, 24-, and 52-weeks post-randomization to assess wound healing, ulcer recurrence, and the incidence of amputation. The items to be measured and the time window of data collection are shown in Fig 1.

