### Statistical analysis

R software will be utilized to conduct statistical analyses. The multiple imputation approach will be utilized to address missing data. Statistical analysis will be conducted using an intention-to-treat approach. Specifically, the chi-square test will be utilized to evaluate the primary outcome measure, namely the wound healing rate at 12 weeks. For sparse data, Fisher’s exact test will be used. Logistic regression analysis will be conducted to investigate potential confounding factors that may influence wound healing. Confounding factors, such as sex, age, history of diabetes, ulcer categories, wound area, and infection status, will be adjusted to ensure the reliability of the findings. Subgroup analysis will be conducted according to age, wound categories, and wound area. The reduction rate of ulcer area and wound healing time at 12 weeks were evaluated using either the independent t-test or the Mann-Whitney, contingent upon meeting the assumptions for parametric analysis. Furthermore, the chi-square test will be applied to assess the ulcer recurrence rate and the amputation rate. Kaplan-Meire survival analysis will be performed to compare wound healing between the two groups, with the log-rank test used for statistical comparison. Unadjusted and adjusted Cox proportional hazards models were employed to evaluate the association between TOT therapy and wound healing. Multivariable models were adjusted for covariates such as age, sex, history of diabetes, ulcer categories, wound area, and infection status. A significance level of P < 0.05 will be considered statistically significant.

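### Time to ulcer healing has two competing analyses with no stated precedence, and one of them (t-test or Mann-Whitney) does not suit wounds still open at week 12

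*Protocol article*

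**What the plan says.** The Secondary outcome list defines time to "ulcer healing: duration until complete wound" closure. Under Follow-up, participants are treated "until complete wound healing occurs or for a maximum duration of 12 weeks".

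The Statistical analysis section then deals with healing over time in two places. One sentence groups healing time with ulcer area reduction: "wound healing time at 12 weeks were evaluated using either the independent t-test or the Mann-Whitney", the choice depending on whether parametric assumptions hold. Later in the same paragraph, Kaplan-Meier "survival analysis will be performed to compare wound healing between the two groups", with a log-rank test and with unadjusted and adjusted Cox models. Only the first sentence names healing time; the survival methods are attached to wound healing in general. Every test is judged at P < 0.05. The section also commits to intention-to-treat analysis and to multiple imputation for missing data. It gives no rule for a wound still open at week 12 in the t-test or Mann-Whitney.

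**The concern.** A duration until closure does not exist for a wound that has not closed. A t-test or Mann-Whitney needs a value for everyone it compares, so someone must decide what to do with the open wounds, and the text does not decide it.

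If open wounds are left out, the test compares two groups selected by the outcome, and selected to a different extent in each arm. Wounds that close on TOT but would have stayed open on sham enter only the TOT side. If they close later than the average sham closure, they lengthen the TOT mean, and an effective treatment can look slower.

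Because log-rank and Cox results will also be produced, the trial could report two P values for one outcome that disagree for technical reasons, with nothing written in advance to say which one counts.

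**Working it through.** **Inputs.** The Sample size calculation section assumes a "30% relative improvement in the wound healing rate, i.e., from 60% to 78" per cent, a "two-sided test with a significance level (α) of 0.05 and a statistical power (1-β) of 0.8", and that "each experimental and control group should comprise approximately 100 participants, totaling 250 participants when accounting for an expected dropout rate of approximately 20" per cent. Allocation is 1:1. The protocol gives no distribution of healing times, so every distribution below is an assumption.

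**The plan's own figure.** Unpooled two-proportion formula: n = (1.96 + 0.8416)² × (0.60 × 0.40 + 0.78 × 0.22) / 0.18² = 7.849 × 0.4116 / 0.0324 = 99.7, so 100 per arm. Allowing for dropout, 100 / 0.80 = 125 per arm, 250 in total. The stated figure is reproduced.

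**Participants without a healing time at week 12.** Sham 1 − 0.60 = 40%; TOT 1 − 0.78 = 22%. That is 40 and 22 per 100, before dropout and early exits.

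**Exponential illustration.** Weekly rates are −ln(0.40)/12 = 0.0764 and −ln(0.22)/12 = 0.1262, a hazard ratio of 1.65.

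- Mean time among healers, 1/λ − 12S/(1 − S), where S is the proportion unhealed: sham 13.10 − 8.00 = 5.10 weeks; TOT 7.92 − 3.38 = 4.54 weeks. Difference 0.56 week.
- Mean time unhealed over 12 weeks, everyone included, (1 − S)/λ: sham 7.86 weeks; TOT 6.18 weeks. Difference 1.68 weeks.

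Restricting to healers therefore leaves about a third of the difference (0.56 / 1.68).

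**Log-rank power by formula.** Expected healings at 100 per arm: 60 + 78 = 138. Power = Φ(√(138/4) × ln 1.652 − 1.96) = Φ(0.99) = 0.84. At 125 per arm (172.5 healings) it is 0.91.

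**Simulation.** 100 per arm, 1,500 trials per row, times rounded up to whole weeks to match the weekly photographs, administrative censoring at week 12 only. Every row has 60% v 78% healed by week 12. Entries in the last four columns are the proportion of trials with P < 0.05.

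| Assumed pattern | Healers' mean, sham v TOT (weeks) | Healers only: t / Mann-Whitney | Unhealed ranked worst: Mann-Whitney | Unhealed set to 12 weeks: t | Log-rank |
|---|---|---|---|---|---|
| Weibull shape 1 | 5.60 v 5.07 | 0.16 / 0.15 | 0.80 | 0.77 | 0.83 |
| Weibull shape 1.5 | 6.87 v 6.35 | 0.16 / 0.16 | 0.80 | 0.74 | 0.85 |
| Weibull shape 2 | 7.77 v 7.28 | 0.18 / 0.18 | 0.80 | 0.72 | 0.83 |
| Weibull shape 3 | 8.88 v 8.51 | 0.15 / 0.15 | 0.79 | 0.64 | 0.82 |
| Lognormal, accelerated time (sigma 0.8) | 7.07 v 6.09 | 0.51 / 0.51 | 0.94 | 0.93 | 0.92 |
| More healers, same timing | 7.52 v 7.50 | 0.06 / 0.06 | 0.63 | 0.46 | 0.75 |
| Extra 18% heal in weeks 8–12 | 7.49 v 8.19 | 0.30 / 0.30 | 0.30 | 0.09 | 0.55 |

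The four Weibull rows are the proportional-hazards cases. Other runs under proportional hazards put healers-only power as low as 0.14, and power with unhealed wounds set to 12 weeks at 0.78 to 0.80 in unrounded time.

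**Direction.** The healers' mean favours sham in 17–20% of trials under proportional hazards, 2% in the lognormal case, 48% with the same timing, and 92% when the extra closures are late. In the late case it is significantly wrong in 30%. The shift follows by hand: (18/78) × (10.5 − 7.5) = 0.69 week, where 10.5 and 7.5 are the rounded-up means of closures spread evenly over weeks 8–12 and 2–12. Other versions of the late pattern gave the wrong direction in 90–99% of trials and significantly wrong in 25–54%.

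**The case against.** The strongest reply is that a suitable analysis is already planned. Kaplan-Meier, log-rank and Cox methods handle open wounds, and ranking of secondary analyses is often left to an analysis plan, which is not shown here. This stands in part: a reader might infer that the trial has no valid time-to-healing analysis, and that would be wrong. What remains is that the article itself fixes an unsuitable test for healing time beside the suitable one.

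A reader might also infer that the t-test or Mann-Whitney will be run on healers only. The text does not say so, and its intention-to-treat commitment points the other way. Ranking unhealed wounds worst costs the Mann-Whitney only about 3 to 5 points of power under proportional hazards. But no such rule is written, so the healers-only reading is not excluded either.

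A third inference is that multiple imputation would invent closure times for wounds seen to be open. The plan applies imputation to missing data, and an observed open wound has a known status. This is a gap to close in the wording, not an error in the text.

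Finally, the power figures depend on assumed distributions, and a reversed direction is the expected result only if the extra closures come late, which nothing in the protocol supports or excludes. That is correct and limits what can be claimed.

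**Conclusion.** The point holds as a should-fix on a secondary outcome. Two analyses of time to healing are stated, neither is given precedence, and one does not suit an outcome that 40% of sham and 22% of TOT participants would lack at week 12.

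The size is conditional. On a healers-only reading under proportional hazards at 100 per arm, power is about 0.14 to 0.18 against 0.82 to 0.85 for log-rank; across the other patterns in which the extra closures are not placed late, it runs from 0.06 to 0.51. If unhealed wounds are ranked worst or set to 12 weeks, the loss under proportional hazards is much smaller: Mann-Whitney about 0.80, t-test about 0.64 to 0.80. All these figures assume no early exits.

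A general loss of power or a reversed result should not be asserted as what the plan will produce. The primary chi-square comparison of the healed proportion and the sample size are unaffected.

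**What to change.** 1. Delete healing time from the t-test/Mann-Whitney sentence, leaving that sentence for ulcer area reduction.
2. Name the log-rank test and Cox model already planned as the analysis of time to ulcer healing, on all randomised participants, with wounds still open at week 12 censored there.
3. State that wounds known to be open are not given imputed healing times.
4. State how participants who leave under the criteria in Withdrawal of individual subjects are analysed, in particular those with less than 20% reduction at four weeks or with indications for amputation. These exits are related to outcome, so censoring at exit would bias the log-rank and Cox results. Examples are to keep recording healing status to week 12, or to count them as unhealed to week 12.

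A healers-only mean may stay as a descriptive figure labelled as such. Restricted mean time unhealed is an optional summary.

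The text change is a few words removed and a few sentences added, with no new patients. Recording status after exit, if chosen, takes some follow-up effort. The downside is the loss of a simple tested figure for mean days to heal.

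### Percent ulcer-area reduction: at the planned healing rates the data-driven choice of test serves no purpose, and leaving out baseline wound area may cost some power (minor)

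*Protocol article*

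**What the plan says.** All references are to the protocol article; no statistical analysis plan is shown.

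- **Statistical analysis.** Ulcer-area reduction is compared by "either the independent t-test or the Mann-Whitney, contingent upon meeting the assumptions for parametric analysis". No covariate is named for this comparison. Wound area is a covariate in the logistic and Cox models for healing, and it is also a subgroup factor.
- **Secondary outcome.** The endpoint is the "percent change in wound size after 12 weeks" of treatment, listed first among the secondary outcomes.
- **Primary outcomes.** Healing means complete epithelial closure by week 12. A wound that heals and stays closed therefore has a reduction of exactly 100%.
- **Sample size calculation.** "Assuming a baseline wound healing rate of 60% in the standard treatment group over a 12-week period", the section hypothesises a "30% relative improvement in the wound healing rate, i.e., from 60% to 78" per cent. It uses a "two-sided test with a significance level (α) of 0.05 and a statistical power (1-β) of 0.8" and arrives at "approximately 100 participants, totaling 250 participants when accounting for an expected dropout rate of approximately 20" per cent. It also cites control healing rates of 42.8% (a published study) and 69% (the group's own earlier research).
- **Inclusion criteria.** Eligible ulcers measure 1 to 20 cm².

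**The concern.** The plan leaves the test open until the data are seen, yet its own healing rates already settle the question. With 60% and 78% of values tied at 100% and the rest in a lower tail, the data cannot look normal. The rule then adds an analyst's decision and nothing else.

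The comparison also makes no use of baseline area as a covariate. Area is collected, spans a twenty-fold range, and is treated as relevant to healing in the plan's other models. Dividing by baseline area rescales the outcome, but it does not remove a relation between initial size and the chance of closing.

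At stake are some power and a clear effect measure for one secondary outcome. The validity of the trial is not at stake.

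**Working it through.** **1. The plan's own sample size.** Inputs are 60% v 78%, two-sided alpha 0.05 and power 0.8, with participants "randomly assigned in a 1:1 ratio to either receive TOT or sham oxygen therapy".

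- Unpooled: n = (1.960 + 0.842)² × (0.60×0.40 + 0.78×0.22) / 0.18² = 7.849 × 0.4116 / 0.0324 = 99.7, so 100 per arm.
- Pooled (mean proportion 0.69): n = [1.960×√(2×0.69×0.31) + 0.842×√0.4116]² / 0.0324 = 102.4, so 103 per arm.
- Dropout: 100 / 0.8 = 125 per arm, 250 in total.

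The stated figures reproduce.

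**2. How often a median is exactly 100%.** With n = 100 this needs at least 51 healed wounds, so the probability is P(Bin(100, p) ≥ 51).

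| Healing rate p | Probability |
|---|---|
| 42.8% (cited control rate) | 0.06 |
| 60% (planned control rate) | 0.973 |
| 69% (cited control rate) | above 0.999 |
| 78% (planned TOT rate) | above 0.999 |

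At the planned rates both medians are 100% with probability of about 0.97, and simulated trials gave about 97%. With 125 per arm the control figure is 0.988.

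**3. Power of the candidate tests.** There were 2,000 simulated trials per row, with 100 per arm, 60% v 78% healing and complete data. Healed wounds score 100%. The following are assumptions, because the document gives none of them:

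- unhealed wounds have a mean reduction of 60% and SD 30 points, capped at 99%;
- the benefit of TOT in unhealed wounds is 0 or 10 points;
- baseline area is uniform on the log scale;
- the log-odds of healing change by 0 to −1.5 per SD of log area, and the mean reduction in unhealed wounds moves by 8 times that slope.

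The adjusted analysis regresses the ranks on arm and baseline log area. Power is in per cent, with a simulation standard error of about √(0.78×0.22/2000) = 0.9 points.

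| Slope | Benefit in unhealed | Chi-square on healing | t-test | Mann-Whitney | Adjusted ranks | Gain over Mann-Whitney |
|---|---|---|---|---|---|---|
| 0 | 0 | 80.1 | 58.5 | 77.8 | 77.8 | 0.0 |
| −0.5 | 0 | 79.1 | 57.2 | 76.8 | 79.3 | 2.5 |
| −1.0 | 0 | 79.0 | 55.8 | 76.2 | 84.0 | 7.8 |
| −1.5 | 0 | 81.4 | 57.9 | 77.6 | 89.0 | 11.4 |
| 0 | 10 | 80.3 | 82.0 | 84.3 | 84.2 | −0.1 |
| −0.5 | 10 | 78.9 | 82.4 | 83.6 | 85.3 | 1.7 |
| −1.0 | 10 | 77.8 | 80.5 | 82.6 | 89.0 | 6.4 |
| −1.5 | 10 | 79.7 | 79.2 | 81.9 | 92.5 | 10.6 |

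A Shapiro-Wilk test rejected normality in every trial checked. With 60% healing in both arms and slope −1.0 (3,000 trials), type I error was 5.4% for the t-test, 5.2% for Mann-Whitney and 5.2% for adjusted ranks.

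**4. Sensitivity to the tail.** With a worse and more spread lower tail (assumed mean reduction 30-40%, SD 40-70 points; log-odds of healing falling by 0.5 to 1.5 per unit of log area; no extra benefit in unhealed wounds), power was:

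- t-test 53-62%;
- Mann-Whitney 77-78%;
- adjusted ranks 78-79%, 82% and 87% as dependence on area goes from weak to strong.

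The gain from adjustment is then about 1, 4-5 and 9-10 points. The t-test's deficit runs from 77 − 62 = 15 to, at the extreme, 78 − 53 = 25 points.

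**The case against.** A reader might infer four stronger things, and the document supports none of them.

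- **That the ceiling and equal medians lose power.** Mann-Whitney does not compare medians. In the table it is 2 to 4 points below the primary chi-square test when the benefit is confined to complete healing, and 2 to 5 points above it when unhealed wounds also benefit.
- **That the t-test loss will occur.** If the check is a formal normality test, the rule leads to Mann-Whitney every time at these rates. The loss is real only if the assumptions are judged met on other grounds, and the article does not say how they are checked. With a 10-point benefit in unhealed wounds the t-test trails by only 1 to 3 points.
- **That the plan will report 100% v 100%.** It names tests and never says that medians are the summary. Such detail may properly sit in an analysis plan that is not shown.
- **That both medians are bound to be 100%.** That rests on the assumed 60%. At the cited 42.8% the control median would rarely be 100%.

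It is also fair to say that an unadjusted test in a randomised trial is valid, that percent change already has baseline area as its denominator, and that healing is analysed elsewhere with area in the model.

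All of this stands and limits the point to a minor one. It does not remove the point, because the article states a method and a selection rule. The stated choice has no use at the planned rates, and an adjusted analysis of data already collected does as well or better.

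**Conclusion.** The point holds as an optional improvement to one secondary analysis. At the planned 60% v 78% healing the parametric condition cannot be met, so the conditional choice should go. Mann-Whitney would be a valid single choice, with about 76-80% power at 100 per arm if the benefit lies only in complete healing.

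The avoidable loss from ignoring baseline area is 0 to about 10 points (11 in the most prognostic scenario run). It is zero if area is not prognostic, and the document gives no figure for that. A t-test, if it were used, would cost about 15-20 points, and somewhat more with a very wide lower tail, but only when the benefit is confined to complete healing.

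These sizes rest on the planned healing rates, complete data and the assumed distribution in unhealed wounds. Type I error and the primary conclusion are not affected.

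**What to change.** Delete the conditional choice for ulcer-area reduction and prespecify one analysis: a proportional-odds (cumulative logit) model of percent area reduction at 12 weeks on treatment arm and baseline log wound area. Report the common odds ratio for a larger reduction with its 95% CI. Beside it, describe by arm the share at exactly 100% and the distribution of reduction among unhealed wounds, so that a reader can see whether the effect lies in closure, in partial shrinkage or in both.

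Without the covariate, this model's score test is essentially Mann-Whitney, so no existing strength is given up. The adjusted power figures above come from the rank regression and indicate the likely gain; they were not computed from the proportional-odds model itself.

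The cost is a change of analysis wording. No new data or participants are needed. The drawback is an effect measure less familiar than a mean difference. If an existing analysis plan already fixes one suitable method, aligning the article's sentence with it is enough.

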### Patient and public involvement

The formulation of the research question, the determination of outcome measures, and the design of the protocol were conducted without the involvement of patients or members of the general public.

## Discussion

Chronic wounds represent a substantial public health challenge on a global scale. The high-altitude environment exacerbates the complexity of the wound healing process. In order to improve wound healing outcomes, various interventions are currently being developed and evaluated in clinical settings. This trial has the potential to provide definite evidence that TOT is an efficacious and safe therapeutic option for patients with chronic wounds in high-altitude regions.

In fact, the efficacy of TOT in promoting the healing of diabetic foot ulcers has been substantiated by a randomized clinical trial [18]. A systematic review and meta-analysis further support these findings, indicating that TOT is a viable treatment option for chronic Wagner 1 or 2 diabetic foot ulcers in the absence of infection and ischemia, with a risk ratio of 1.59 (95%CI 1.07–2.37; *p* = 0.021) [23]. However, it is crucial to acknowledge that previous studies have predominantly focused on the effectiveness of this therapy in mild cases. To date, no research has specifically examined its application in high-altitude populations. The results of this trial may provide valuable insights into the potential benefits of TOT in such settings.

In this study, the standard of care for chronic wounds is established by the attending physicians and is not governed by a standardized protocol. This methodology reflects actual clinical practice. Consequently, it is reasonable to assume that the results can be extrapolated to the broader Chinese population inhabiting high-altitude regions. However, it should be emphasized that the implementation of TOT therapy requires the availability of TOT device, which may pose challenges in resource-limited settings. In fact, the procedure for TOT therapy is relatively straightforward and can be effectively performed by healthcare practitioners following minimal training. Nevertheless, the single-center design of this study may impose limitations on its external validity. Further multi-center studies could potentially strengthen the generalizability and reliability of these findings. Of course, it should be noted that it may be a challenge to recruit enough subjects due to the lower population density at high altitudes.

In conclusion, the results of this trial will provide further evidence to substantiate the efficacy of TOT in the treatment of chronic wounds in high-altitude regions. Further studies may be conducted to elucidate the underlying mechanisms of TOT therapy and assess its applicability across diverse wound categories.

